#### Major adverse events (MAEs)

MAEs are defined as myocardial infarction (MI), stroke, and all-cause death occurring during the postoperative follow-up period.

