**Methods:**

This will be a prospective, multicenter, randomized, parallel-group trial. This study will include 600 patients with great saphenous vein insufficiency (C2–C6) treated with endovenous radiofrequency or laser ablation at 7 high-volume centers. The participants will be randomly assigned to the following groups at a 1:1:1 ratio: the one-month (OM) group, which will wear class II compression stockings (23–32 mmHg) for 1 month after surgery; the three-month (TM) group, which will wear compression stockings for 3 months; and the six-month (SM) group, which will wear compression stockings for 6 months. All the groups will wear the same compression stockings and follow the same instructions for wearing the stockings. The primary outcome is the recurrence of VVs at 12 months; the secondary outcomes include the closure rate of the great saphenous vein, disease-specific quality of life assessed by the Aberdeen Varicose Vein Questionnaire (AVVQ), the Chronic Lower Limb Venous Insufficiency Questionnaire (CIVIQ) score, the Venous Clinical Severity Score (VCSS), the incidence of postoperative complications (pain, ecchymosis, paresthesia, deep vein thrombosis, etc.), and patient compliance. The follow-up times are 1, 3, 6, and 12 months after surgery.

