#### Postoperative complications

Postoperative complications (within 30 days) will include hematoma, ecchymosis, paresthesia, skin burns/paresthesia, phlebitis, infection, and DVT.

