### Sample size and study duration

According to previous studies (27–32) and recent systematic analyses, the 12 month recurrence rate after the thermal ablation of VVs in the lower extremities is approximately 3%–5%. The setting in the OM group is 4% and the non-inferiority threshold *δ* is −6% (17). With a statistical power of 90% and a significant equivalence of 1.7% (one-sided), at least 511 patients (170 in each group) needed to be recruited. However, considering the potential withdrawal rate of 20% and the very low incidence of adverse events in this trial, the total sample size was increased to 600 patients (200 in each group). The patients will be followed up for 12 months, and the study is expected to last for 36 months.

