### Statistical analysis

Analysis will follow the intention-to-treat (ITT) and per-protocol (PP) principles. Continuous outcomes (AVVQ score, VCSS, VAS score, and CIVIQ) will be analyzed using linear mixed models (LMMs) adjusted for baseline values, center, CEAP class, and time. Non-inferiority will be declared for the AVVQ score at 12 months if the upper limit of the 95% CI for the difference (OM-SM or TM-SM) is <*δ* (2.0 points). Recurrence rates will be compared using Kaplan-Meier survival analysis and Cox proportional hazards models. Complications will be compared using chi-square tests or Fisher’s exact tests. Compliance will be summarized descriptively. Subgroup analyses (e.g., by CEAP class, ablation type) are planned. Sensitivity analyses will be performed to assess the impact of missing data. SPSS version 21.0 will be used. *p* < 0.05 will be considered to indicate significance for superiority analyses.

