### Safety considerations

There are no significant health related risks associated with our proposed study. Adverse events (AEs) are unexpected medical events that occur in patients and may or may not be related to a study device. Regardless of whether AEs occur, the AE form should be completed and sent to the principal investigator by email within 24 h. If the principal investigator considers an event to be “study related” (i.e., caused by the implementation of any study procedure), the AE will be further reported to the research ethics committee. Investigators at each center should report any AE according to the requirements of their research ethics committee and the sponsor.

If any damage related to the pressure therapy study occurs during the study, the fund will bear the corresponding treatment costs and provide compensation in accordance with national laws and regulations.

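### No defined safety outcome captures a non-fatal pulmonary embolism or a late deep vein thrombosis once the arms' stocking durations diverge

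*Protocol article*

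**What the plan says.** Two safety outcomes are defined among the secondary outcomes of the protocol article.

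- **Postoperative complications:** "Postoperative complications (within 30 days) will include hematoma, ecchymosis, paresthesia, skin burns/paresthesia, phlebitis, infection, and DVT". The abstract gives a shorter, open-ended list: "the incidence of postoperative complications (pain, ecchymosis, paresthesia, deep vein thrombosis, etc".
- **Major adverse events (MAEs):** "MAEs are defined as myocardial infarction (MI), stroke, and all-cause death occurring during the postoperative follow-up period".

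PE is not named in either definition or anywhere else in the text supplied.

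The Statistical analysis section gives one rule for safety data: "Complications will be compared using chi-square tests or Fisher’s exact tests". It states no comparison for MAEs or for adverse events in general. Under Safety considerations, "the AE form should be completed and sent to the principal investigator by email within 24 h", and events judged related to the study go on to the ethics committee. No tabulation by arm is described there.

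The section on postoperative compression gives every arm the same stockings and the same wearing pattern from the operating room onwards. The arms part only when the one-month group stops.

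**The concern.** The plan counts DVT but not its more serious consequence, while the MAE outcome counts myocardial infarction and stroke, which are arterial. The windows make this matter more. DVT is counted over 30 days, which is essentially the period in which all arms are treated alike. The only adverse-event outcome that runs beyond it contains no non-fatal venous event. For the months in which the randomised durations differ, the plan therefore defines no outcome through which a difference in non-fatal venous thromboembolism could be seen.

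At stake is the completeness of the safety account. A report that followed these definitions to the letter could describe the harms of shorter and longer compression without giving late DVT or non-fatal PE by arm.

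**Working it through.** The plan states no figure on this point, so the first step is to trace each kind of event through the definitions.

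| Event | Complications (30 days) | MAE (whole follow-up) | Adverse event form |
|---|---|---|---|
| Fatal PE | not named | yes, as death | yes |
| Non-fatal PE, DVT also diagnosed by day 30 | yes, through the DVT | no | yes |
| Non-fatal PE by day 30, no DVT diagnosed by then | not named; only if the list is read as open | no | yes |
| Non-fatal PE after day 30, no DVT by day 30 | outside the window | no | yes |
| Non-fatal DVT first diagnosed after day 30 | outside the window | no | yes |

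The last two rows do not depend on whether the complication list is open or closed, because the 30-day limit excludes both events.

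The second step sets the windows against the assigned treatment.

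- Surgery to month 1: all arms wear stockings as instructed. DVT is counted.
- Months 1 to 3: the one-month group has stopped. No non-fatal venous outcome is defined.
- Months 3 to 6: only the six-month group continues. None is defined.
- Months 6 to 12: all arms have stopped, having worn stockings for different lengths of time. None is defined.

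The third step is scale. The sample size comes from the sample size section: "the total sample size was increased to 600 patients (200 in each group". The documents give no PE rate, so the rates p below are assumptions. Expected events are 600 × p, and the chance of at least one is 1 − (1 − p)^600.

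| Assumed PE rate | Expected in 600 | Expected per arm of 200 | Chance of at least one |
|---|---|---|---|
| 0.1% | 0.6 | 0.2 | 45% |
| 0.2% | 1.2 | 0.4 | 70% |
| 0.5% | 3.0 | 1.0 | 95% |

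Counts this small cannot support a test. Suppose three PEs all fell in one arm. With 200 patients per arm, the chance of that under no difference is 3 × (200 × 199 × 198) / (600 × 599 × 598) = 3 × 7,880,400 / 214,921,200 = 0.11. No split of three events is more extreme, so Fisher's exact p-value cannot fall below 0.11. An interval is more informative. With no event in 200 patients, the exact two-sided 95% upper limit is 1 − 0.025^(1/200) = 1.8%.

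**The case against.** Several counter-arguments carry weight.

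- **The lists may be open.** The complication list is introduced as what will be included, and the abstract's version trails off. This stands as a possible reading for the first 30 days. It does not help after day 30, and the MAE outcome is worded as a definition.
- **The event is captured elsewhere.** A reader might infer that a non-fatal PE would go unrecorded, or would count only if fatal. The document does not support that: adverse event reporting would pick it up, a DVT diagnosed within 30 days would count the patient, and a fatal PE counts as a death.
- **No MAE test is stated.** A reader might fear a formal finding of no difference in MAEs that leaves PE out. The analysis section compares complications only, so that test is not in the plan. For the same reason, adding PE to the MAE definition alone would put it in a category with no stated comparison.
- **The document does not tie duration to thromboembolism.** Its introduction names pain, edema, bruising and recanalization as the targets of compression, and discomfort and skin irritation as its burdens. So the claim that thromboembolism is the harm most likely to depend on duration is not supported here. The plan does treat thrombosis as relevant, since it counts DVT and excludes patients with a history of it.
- **The article is condensed.** Itemised adverse event tables are often left to a fuller document. That would answer a complaint about missing detail. Here the article states both outcome definitions and their windows, and the gap follows from those.

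**Conclusion.** The point holds in a limited form and is minor. As written, a non-fatal PE without a DVT diagnosed by day 30 enters no clearly pre-specified between-arm safety outcome. No non-fatal venous thromboembolic outcome covers the months after the assigned durations diverge. The second statement is the firmer, because it rests on the stated windows and not on how the complication list is read.

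The size is about 1 to 3 PEs in 600 patients if the rate is 0.2% to 0.5%, which is an assumption. Late DVTs would add to this by a number the documents give no basis for estimating. The consequence is incomplete reporting of harms by arm. Neither the primary outcome nor the power of any stated comparison is affected.

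**What to change.** Define venous thromboembolism as a safety outcome: clinically detected DVT or PE, fatal or non-fatal, from surgery to 12 months, in all arms. Take the events from the adverse event reports already collected. Report counts by arm with exact confidence intervals, and name the outcome in the Statistical analysis section alongside the complications compared by Fisher's exact test. Keep the 30-day DVT count as a separate perioperative figure, so that a 12-month PE count is not combined with a 30-day DVT count.

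The cost is one outcome definition, a phrase in the analysis section and one more case report form item. Reported event counts will be slightly higher. A fatal PE will appear both here and among deaths, which a footnote can state. The sample size, randomisation and primary analysis are unchanged. The gain is a complete account of harms; the comparison will remain descriptive in practice.

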#### Trial duration

On the basis of the experimental standard criteria, the case distribution of each central hospital, and previous similar trials, this study is expected to be completed in approximately 24–36 months (Figure 2; Supplementary File S1).

**Figure 2 fig2:**
[figure not shown]
The trial protocol: The baseline and follow up questionnaires of this trials, including the schedule of enrolment, interventions, and assessments. VAS, Visual Analog Scale; VCSS, Venous Clinical Severity Score; AVVQ, Aberdeen Varicose Vein Questionnaire; CIVIQ, Chronic Lower Limb Venous Insufficiency Questionnaire.

### Baseline

Each research center will have a fixed medical staff (doctors or nurses from the surgical team) that is responsible for collecting information and conducting follow-up visits, one researcher who is responsible for collecting information, and another researcher who is responsible for assessing the quality of the questionnaire. All researchers will receive unified training before formal follow-up. At baseline, we will collect main demographic data, surgery-related data, and perioperative complication data from each patient and complete the collection of questionnaire data.

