
### Objectives

The primary objective of this study is to determine the recurrence of VVS at 12 month after thermal ablation in patients with different durations of compressure therapy, assessed by duplex ultrasound scanning and clinical physical examination. The secondary objectives are the saphenous vein (GSV) closure rate at 12 month, the closure failure is defined by a segment of the reopen vein ≥5 cm by ultrasound. The VCSS, AVVQ, CIVIQ scores are compared among the three groups at baseline, 1, 3, 6, and 12 month, as well as the pain scores [using the Visual Analog Scale (VAS)] at baseline, 24 h, and 1 month after surgery. Postoperative complications are recorded in three groups, and the compliance of compressure therapy is investigated.

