### Randomization and blinding

Eligible, consenting patients will be randomized at a 1:1:1 ratio to one of the following groups: the one-month group (OM group, elastic stockings for 1 month), three-month group (TM group, elastic stockings for 3 months), and six-month group (SM group, elastic stockings for 6 months) using a central, computer-generated, stratified block randomization sequence via a secure randomization-generated web-based system. Patients and physicians cannot be blinded owing to the nature of the intervention (duration visible to the patients). The outcome assessors (Duplex ultrasound technicians, QoL questionnaire administrators) and statisticians will be blinded to group allocation.

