### Primary outcome

The primary outcome is the recurrence of target VVs at 12 months (21, 22). New recurrence is defined as the postoperative appearance of VVs that did not exist in the VV area in the lower limbs before surgery; primary recurrence is defined as the reappearance of VVs that existed in the VV area before surgery during follow-up. Both types of recurrence are defined as postoperative recurrence.

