### Data collection and confidentiality

Trained researchers will collect data by using a unified case report form. Patient demographic data, laboratory results, and surgery-related data will be extracted from the electronic medical records system, and baseline CEAP classification, VCSS, AVVQ, EQ-5D scores and ultrasound data will be recorded. All the data will be cross-checked by two independent researchers to ensure accuracy. To reduce the loss rate and ensure that each participant completes the follow-up on time, we will record each participant’s mobile phone number and social media account (WeChat), and the researchers will remind the participants of the follow up before each follow-up time point. Moreover, we will ask each participant about their compliance with compression therapy to assess whether they interrupt or deviate from the intervention plan. The participants will receive a separate trial identification number on the basis of the order of inclusion. All information collected in this study, including electronic and paper questionnaire data, will be securely stored in each center for at least 10 years. All data will be strictly confidential and accessible only to trial team members, and anonymous trial data will be shared with other researchers upon reasonable request.

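### The clinical examination within the primary outcome is not covered by the blinding claim and, as written, falls to surgical-team staff who can know the arm

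*Protocol article*

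**What the plan says.** All of the following is in the Protocol article.

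- **Study design** describes the trial as open-label.
- **Randomization and blinding** states: "Patients and physicians cannot be blinded owing to the nature of the intervention". It then says: "The outcome assessors (Duplex ultrasound technicians, QoL questionnaire administrators) and statisticians will be blinded to group allocation". No clinical examiner is on that list.
- **Baseline** gives each centre "a fixed medical staff (doctors or nurses from the surgical team) that is responsible for collecting information and conducting follow-up visits". It also lists one researcher who collects information and another who checks questionnaire quality. It does not say whether these two are blinded or work outside the surgical team.
- **Objectives** says that recurrence is "assessed by duplex ultrasound scanning and clinical physical examination".
- **Primary outcome** defines recurrence as varicose veins newly appearing or coming back. For the second type: "primary recurrence is defined as the reappearance of VVs that existed in the VV area before surgery during follow-up". No ultrasound criterion is attached; the 5 cm reopening criterion belongs to GSV closure, a secondary outcome.
- **Postoperation compression** has compliance tracked by diaries and questionnaires. **Data collection and confidentiality** adds: "we will ask each participant about their compliance with compression therapy to assess whether they interrupt or deviate from the intervention plan". The person asking is not named.

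**The concern.** Whether varicose veins have reappeared on a leg is partly a matter of judgement. The article protects the scan and the questionnaires by naming blinded roles for them, but names none for the physical examination. The only people it describes as conducting follow-up visits come from the surgical team, and the doctors among them belong to a group that it says cannot be blinded. These staff are fixed at each centre, so what they learn about stocking use at 3 or 6 months can carry forward to the 12-month visit.

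At stake is detection bias in the primary endpoint of a non-inferiority comparison with few events. If recurrences in a shorter-duration arm are called less readily, the arms look more alike and non-inferiority is easier to declare. If they are called more readily, the error runs the other way. The documents give no basis for saying which is more likely.

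**Working it through.** **Step 1: who does what, and is that role stated to be blinded?**

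| Task | Performed by | Stated as blinded? |
|---|---|---|
| Duplex scan | Duplex technicians | Yes |
| Quality-of-life questionnaires | Questionnaire administrators, not otherwise identified | Yes, but not tied to any staff in Baseline |
| Follow-up visits and information collection | Surgical-team doctors or nurses; a researcher also collects information | No; physicians are stated to be unblinded, nurses are not mentioned |
| Clinical examination for recurrence | Not named; visits are conducted by surgical-team staff | No |
| Questions on stocking use | Not named | No |

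The fourth row is the gap. Clinical examination is part of how the primary outcome is assessed, yet no blinded role covers it. For the questionnaires and the stocking questions, the table shows an assignment left open.

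**Step 2: how sensitive is the comparison to a few calls?** The article states no figure for this, so there is none to reproduce. Inputs from the Sample size section are a recurrence rate of 4%, a margin of 6 percentage points in absolute size, 170 patients per group before the dropout allowance and 200 after it, and a one-sided level of 1.7%. The 170 is taken as stated.

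- Expected recurrences per arm: 0.04 × 170 = 6.8.
- Assumed shift of 3 calls in one arm: 3/170 = 1.8 points; 1.76/6 = 29% of the margin.
- Assumed shift of 4 calls: 4/170 = 2.4 points; 2.35/6 = 39% of the margin.
- With 200 per arm: 0.04 × 200 = 8 expected; 3/200 = 1.5 points (25% of the margin) and 4/200 = 2.0 points (33%).

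**Step 3: effect on the false-positive rate under assumed under-detection.** Take true recurrence of 10% in a shorter arm, exactly at the margin, and 4% in the reference arm, with 170 per arm. If a fraction s of shorter-arm recurrences is detected, the observed rate is p = 0.10 × s. With unpooled variance and the normal approximation:

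- SE = √[(0.04 × 0.96 + p(1 − p))/170]
- Pr(declare non-inferiority) = Φ[(0.06 − (p − 0.04))/SE − z], where z is the 98.3rd percentile of the standard normal, 2.12.

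| s (assumed) | p | Pr(falsely declare non-inferiority) |
|---|---|---|
| 1.0 | 0.10 | 1.7% |
| 0.9 | 0.09 | 4.1% |
| 0.8 | 0.08 | 9.0% |
| 0.7 | 0.07 | 18.3% |

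For example, at s = 0.8, SE = √[(0.0384 + 0.0736)/170] = 0.0257, and Φ(0.02/0.0257 − 2.12) = Φ(−1.34) = 9.0%.

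This illustrates sensitivity and does not predict bias: full detection in the reference arm and every value of s below 1 are assumptions.

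**The case against.** The strongest reply is that the sections can all be true together. Blinding is promised for roles, and Baseline lists two researchers besides the surgical-team staff. Either could be the blinded questionnaire administrator, and the Follow-up section has a researcher assist with data collection. Nothing says that surgical staff scan, administer questionnaires or decide recurrence. The duplex component is blinded, and a scan is scheduled even for patients followed remotely. No arm is due to wear stockings at 12 months, so the leg itself should not give the arm away. This is also a condensed article whose schedule figure is not shown, and duties at each visit are often set out in a fuller document.

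Much of this stands. A reader might infer that the surgical team also asks about stocking use; the text says only "we will ask each participant about their compliance with compression therapy" and does not identify who asks. A reader might infer that the questionnaires are collected unblinded; the two researchers leave that open. A reader might say that half of the primary outcome is unblinded; the article does not say how scan and examination combine, so no share can be given. For patient-reported scales, knowledge of the arm enters mainly through the patient, and no change of staff removes that. The 3 to 4 shifted calls amount to about half of an arm's expected events, all in one direction, which is a hypothetical case.

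The reply does not answer the point about the clinical examination. The article itself lists the blinded roles, omits the examiner, and assigns visits to surgical-team staff. The gap comes from what it states and not from detail left to another document.

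**Conclusion.** The point holds for the clinical component of the primary outcome. That component is outside the blinding claim and, as the sections stand, would fall to staff who can know the arm. For the questionnaires and the stocking-compliance questions, the documents do not say who does what, so the sections need reconciling; a flat contradiction is not shown.

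The possible size is material because events are few, as the working shows, but it depends on an assumed number of shifted calls or an assumed detection rate. Two things remain unknown: how examination and scan are combined into a recurrence call, and the direction of any bias. The plan should be changed on this point, with medium confidence in how much it matters.

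**What to change.** Reconcile the Objectives, Randomization and blinding, Baseline, and Data collection and confidentiality sections as follows.

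1. State that the already-blinded duplex assessor makes and records the 12-month recurrence call, scan plus inspection of the limb, before any compliance question or diary review. Add this role to the list of blinded assessors.
2. Ask patients not to mention how long they wore stockings. Since the longest assigned period ends at 6 months, no arm is due to wear them at this visit. For patients followed remotely, the inspection can be done at the scheduled ultrasound appointment.
3. Where the two researchers already planned per centre allow it, let one collect compliance data and the other administer the questionnaires, with compliance collected last. This should not be mandatory: requiring a questionnaire researcher outside the treating team may need extra staff, and one of the two is already assigned to questionnaire quality.

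At the least, the article should state who performs the 12-month clinical examination and whether that person is blinded.

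**Cost:** minor scheduling effort and brief training of duplex assessors in the inspection; items 1 and 2 only reassign or reorder planned work. **Remaining limit:** patient-reported scales stay open to bias because patients know their arm.
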